#### Sample size and statistical analyses

Primary analysis: sample size calculations are performed for a two-sample *t* test for comparing the Bayley Scale of Infant and Toddler Development, Third Edition, cognitive scale between the intervention (SSC) and control (SC) groups at 2 years of corrected age. To obtain a power of 80% for detecting a difference of 7.5 in mean score, using SD = 15 and significance level α = 0.05, 64 preterm infants are needed in each group. To allow for withdrawals, the sample size is set to 68 in each group.

Secondary analysis: differences between the SSC and SC groups for continuous variables will be analyzed using two-sample *t* tests, or Mann-Whitney *U* tests for data with non-normal distributions. Categorical variables will be analyzed by the Pearson chi-square test or Fisher’s exact test. *P* values <0.05 are considered statistically significant. Due consideration of multiple testing will be made when interpreting the results. All data will be presented and analyzed in accordance with the updated CONSORT guidelines for randomized trials [39].

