### Aims

#### Primary aim

To study the effect of early SSC versus standard care (SC) for very preterm infants (28^0^–31^6^ weeks) on cognitive scores at 2 years corrected age, measured with the Bayley Scales of Infant Development, Third Edition (Bayley-III).

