#### Secondary aims

To assess safety of the intervention by measuring incidence of hypothermia (temperature <36 °C) or respiratory failure during the first 2 hours of life.To estimate the effect of the intervention on complications to prematurity (intraventricular hemorrhage (IVH) or periventricular leukomalacia (PVL), seizures, necrotizing enterocolitis (NEC), treatment for persistent ductus arteriosus (PDA), and bronchopulmonary dysplasia (BPD)).To estimate the effect of the intervention on physiological stability during the first 24 hours.To estimate the effect of the intervention on maternal mental health at discharge from the NICU and when the child’s corrected age is 3 months and again at the corrected age of 2 years by using the State-Trait Anxiety Inventory (STAI).To investigate if the intervention affects the fidgety type of general movements and detailed aspects of the early motor repertoire at the corrected age of 3 months, using the General Movement Assessment (GMA) and the Assessment of Motor Repertoire – 2 to 5 months (AMR).To estimate the effect of the intervention on neurodevelopmental outcomes including cognition, language, and motor function at the corrected age of 1 year, and language and motor function at the corrected age of 2 years assessed with Bayley-III.To investigate the effect of the intervention on social and emotional competence at the corrected age of 3 months and at 2 years with the Ages & Stages Questionnaire - Social-Emotional

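### The only primary comparison named, an unadjusted t test on 2-year scores, leaves unused the masked 1-year Bayley score and the randomisation stratum; using them is a cheap improvement of modest size

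*Protocol article*

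**What the plan says.** The primary aim concerns the effect "on cognitive scores at 2 years corrected age, measured with the Bayley Scales of Infant Development, Third Edition (Bayley-III"). In the section Sample size and statistical analyses, the paragraph labelled as the primary analysis states that "sample size calculations are performed for a two-sample *t* test"; what is compared is the Bayley-III "cognitive scale between the intervention (SSC) and control (SC) groups at 2 years of corrected age". The target is a 7.5-point difference with 80% power. With a standard deviation of 15 and a 5% significance level, the article concludes that "64 preterm infants are needed in each group". The number is then raised to cover loss: "To allow for withdrawals, the sample size is set to 68 in each group". No other primary method is named, and no covariate is mentioned.

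Two pieces of information have no stated role in that comparison:

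- **The 1-year score.** The Secondary aims include "neurodevelopmental outcomes including cognition, language, and motor function at the corrected age of 1 year", and Table 1 schedules the Bayley-III at both 1 and 2 years corrected age. The outcome section says that the occupational therapist who tests at both ages does not know the allocation.
- **The stratum.** The section Randomization and allocation concealment stratifies by gestational age, below and from 30 weeks.

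**The concern.** A two-sample t test at 2 years drops every child without a 2-year score, including those already tested at 1 year on the same scale under masking. Two things are at stake.

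- **Power.** The allowance for loss is 4 of 68 per group over a follow-up of 2 years corrected age. Loss beyond that comes off the 80% target, and the 1-year score could recover part of it.
- **Bias.** Parents know the allocation. If families of children who do poorly at 1 year leave at different rates in the two arms, the children seen at 2 years are no longer comparable. A model of both visits corrects for this as long as loss depends only on arm and observed scores.

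In addition, an analysis that omits a factor used to stratify the randomisation gives up whatever precision that factor offers. The article does not say how prognostic the stratum is, so no figure is attached to this part.

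**Working it through.** **Inputs from the article:** difference 7.5, SD 15 (so 0.5 SD), α 0.05, power 80%, 64 evaluable and 68 randomised per group. Sidedness is not stated; two-sided is assumed because it reproduces the 64.

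**Assumed inputs (not in the article):** correlation ρ between 1-year and 2-year scores of 0.3 to 0.7; loss rates above 5.9%; the loss mechanisms in step 4. Infants are treated as independent, so twin clustering is not in these figures.

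**1. The plan's own figure.** The exact noncentral t calculation gives 63.77, so 64 per group, with 80.1% power. The implied loss is 4/68 = 5.9%, and 64/(1 − 4/68) = 68. With no loss, 68 per group gives 82.5%. Both stated sample sizes reproduce.

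**2. Effective sample size when the 1-year score is used.** Let n₂ children per arm be seen at 2 years and n₁ at 1 year, with loss only between the visits. The maximum-likelihood estimate of the 2-year mean has variance SD² × [(1 − ρ²)/n₂ + ρ²/n₁], so

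n_eff = 1 / [(1 − ρ²)/n₂ + ρ²/n₁].

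Example: 20% loss, ρ = 0.5, n₂ = 54.4, n₁ = 68. Then n_eff = 1/(0.75/54.4 + 0.25/68) = 57.3. Power is 75.6%, against 73.4% for the t test.

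**3. Power (%), if every lost child has a 1-year score.**

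| Loss by 2 years | t test | ρ = 0.3 | ρ = 0.5 | ρ = 0.7 |
|---|---|---|---|---|
| 5.9% | 80.1 | 80.4 | 80.7 | 81.3 |
| 10% | 78.3 | 78.7 | 79.4 | 80.4 |
| 20% | 73.4 | 74.2 | 75.6 | 77.7 |

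The gain is about 0.2 to 1.2 points at the implied loss and 0.8 to 4.4 points at 20%. These are upper bounds. If only half of the lost children were seen at 1 year, the gain at 20% loss falls to 0.4, 1.2 and 2.4 points.

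**4. Bias of the completer comparison.** When loss depends only on the 1-year score,

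bias = ρ × SD × (difference between arms in the mean standardised 1-year score of the retained children).

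- *Same dependence and same rate in both arms (15%):* the two shifts cancel. Simulation with a true difference of 7.5 returned 7.4 to 7.5.
- *Same dependence, unequal rates (10% and 20%):* 7.2, 7.0 and 6.9 for ρ = 0.3, 0.5 and 0.7, a bias of 0.3 to 0.6 points.
- *Dependence in one arm only, random loss at the same rate in the other:* with an odds ratio of 2 per SD lower and 10% loss, the retained children shift by 0.066 SD, and 0.3 × 15 × 0.066 = 0.3 points. With an odds ratio of 3 and 20% loss the shift is 0.186 SD, and 0.6 × 15 × 0.186 = 1.7 points. The simulated type I error runs from about 5% to 9% over this range. The most extreme corner tried (ρ = 0.7, odds ratio 3, 20% loss) reaches 1.9 points and about 10%.

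The two-visit estimator is unbiased in all these cases, apart from simulation noise. That follows by construction, because the simulated loss depends on nothing but arm and the 1-year score.

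**The case against.** The strongest reply is that the sentence gives the basis of the sample size. It does not lay down a complete-case rule, and nothing in the article excludes children without a 2-year score, bars imputation or rules out a supporting model. Handling of missing data is commonly left to a statistical analysis plan, which is not shown. This stands in part: a reader might infer that the article has fixed a completer-only analysis, and the text does not go that far. What remains is that this is the only primary method named, under a label that reads as the primary analysis, and a better one is available from data already scheduled.

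A reader might also infer that the trial is underpowered because of this choice. It is not: loss within the allowance leaves 80.1%, and the article gives no attrition rate that would take it lower.

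Nor can it be inferred that the primary result will be biased. Loss related to early development is not enough; it must differ between arms. The intervention lasts up to 2 hours and later hospital treatment is stated to be the same, so arm-specific loss a year or more later is a conjecture. Against that, parents are unmasked, and the Discussion concedes that knowing the allocation may alter their behaviour.

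Finally, children who die or withdraw before 1 year have no Bayley score and gain nothing from the change. That is correct and limits the benefit.

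**Conclusion.** The point holds as a low-cost improvement to the named method, not as an error in any stated figure. The power gain is about 1 point or less at the loss the plan allows for, and about 1 to 4 points at 20% loss if ρ is 0.3 to 0.7 and every lost child was seen at 1 year.

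Protection against bias is the better argument, but it is conditional: about 0.3 to 1.7 points, or 4 to 23% of the 7.5-point target (0.3/7.5 and 1.7/7.5), when loss depends on the 1-year score in one arm only, and essentially nothing when the mechanism is the same in both arms. The correlation, the loss rates above 5.9% and the loss mechanisms are all assumptions from outside the article.

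**What to change.** Prespecify as the primary analysis a likelihood-based model of the Bayley-III cognitive score at 1 and 2 years, with arm-by-visit and gestational-age-stratum terms, an unstructured covariance across visits, and allowance for twins (for example a mother-level random effect, since twins share an allocation). The primary contrast is the arm difference at 2 years, so the question asked does not change. The 1-year score should enter as an outcome and not as a covariate, because it is measured after randomisation and may itself carry part of the effect. Include every randomised infant with at least one Bayley assessment, and keep the 2-year completer comparison as a sensitivity analysis.

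The cost is a paragraph in the analysis plan and slightly more analysis work; no new data, visits or infants are needed. The downside is reliance on missing-at-random given arm and the 1-year score: if loss depends on the unseen 2-year score itself, the model does not repair it. The article reports 27 infants included by June 2016 against 2 × 68 = 136 planned, so at that date the change could still be fixed before most 2-year scores existed. If an analysis plan already does this, confirming it is enough.

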## Methods/Design

### Project context

The study is currently being carried out at St. Olav’s University Hospital in Trondheim. Trondheim is the third largest city in Norway, and St. Olav’s Hospital serves a population of almost 446,000 and is a tertiary care center for preterm infants <30 weeks of gestation. Approximately 50 infants with GA <32 weeks are born every year at St. Olav’s Hospital.

The NICU at St. Olav’s Hospital has 21 beds, with seven beds for intensive care, seven intermediate, and seven in a step-down unit. Altogether, there are 107 nurses (many part-time) and six consultants working in the NICU. The maternity ward has two sections with seven delivery rooms each and about 120 midwives employed.

Delivery rooms are in the same building as the NICU, but on separate floors (fifth and second floor, respectively). The operating room and the postoperative ward are in the same building and at the same floor as the NICU.

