### Study population

Singleton and twin preterm infants with GA 28^0^–31^6^ and a BW >1000 grams in a stable medical condition delivered either vaginally or by C-section are candidates for inclusion. Twins are randomized to the same intervention. Infants with severe malformations not compatible with life, or requiring surgery within hours to days after birth (e.g. esophageal atresia, abdominal wall defects or neural tube defects), will be excluded.

Infants who need intubation and mechanical ventilation, or CPAP with more than 40% oxygen to maintain a saturation above 90% at 10 minutes of age, are excluded. Mothers have to be awake (not under general anesthesia) during C-section.

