**Fig. 1 Fig1:**
[figure not shown]
Flowchart illustrating the first 2 hours after birth

All infants with a BW <1500 g, irrespective of randomization, are given parenteral nutrition (glucose and amino acids) after the initial stabilization. Infants with a GA <30 weeks receive CPAP, infants ≥30 weeks get CPAP if clinically indicated. If necessary, surfactant can be administered via a thin catheter in the trachea during spontaneous breathing on CPAP (“surfactant without intubation” (SWI) if oxygen requirement exceeds 35% on CPAP and/or the infant has signs of moderate to severe respiratory distress. After the infant is stabilized in skin-to-skin position on the mother’s chest (SSC) or in a closed incubator and transferred to the NICU (SC), the infant is evaluated again (checkpoint 2) according to the checklist (Fig. 1).

Infants in the intervention group are offered SSC up to 2 hours after delivery – in the delivery room after vaginal delivery, or in the recovery room after C-section. A consultant and a neonatal nurse are responsible for the infant, while a midwife takes care of the mother. After C-section, the same personnel from the NICU and from the maternity ward are present in addition to specialist nurses from the postoperative ward. When the infant is stabilized on the mother’s chest, the consultant can leave the DR or postoperative ward in agreement with the neonatal nurse in charge. The consultant is nearby and easily reachable by telephone.

Further treatment during the hospitalization does not differ between groups. According to the unit’s guidelines, both mothers and fathers have unrestricted access to the NICU and are encouraged to have as much skin-to-skin contact with their preterm infant as possible.

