#### Clinical registration

A case report form (CRF) has been prepared in cooperation with the Unit for Applied Clinical Research at the Norwegian University of Science and Technology (NTNU). The CRF is divided into three parts.On admission and the first 24 hours:Background data which are recorded are: mode of delivery, GA, sex, Apgar scores at 1, 5 and 10 minutes, birthweight, length, head circumference, maternal cause of preterm delivery (preeclampsia, breech position, rupture of membranes, premature contractions or infection), fetal cause of preterm delivery (growth retardation, non-reassuring CTG registration), and antenatal steroids (full or incomplete course).Observations and interventions which are recorded during the first 24 hours are: oxygen saturation and requirement, mode of breathing support (hourly), surfactant administration, time of SSC after birth and any cause for interrupted SSC before 120 minutes, age at the first feed (gavage or oral), any intravenous infusion, transcutaneous carbon dioxide and total amount of enteral and parenteral nutrition given. Blood pressure is measured once during the first 120 minutes.Adverse events: the safety is closely monitored by the consultant and the neonatal nurse present. It will be registered as an adverse event if body temperature drops <36.0 C° or if the infants have signs of any respiratory failure requiring interventions in addition to an interruption of SSC and transfer to the NICU for a higher level of monitoring and/or respiratory support.During hospitalization:Variables recorded are: daily weight, age on removal of feeding tube, time in skin-to-skin position every day, all nutrition (parenteral and enteral), any insulin given, any surgery, mechanical ventilation (mode and duration), CPAP/bilevel positive airway pressure (BiPAP) (duration), supplemental oxygen and/or ventilator support at 28 postnatal days, 36 and 40 weeks postmenstrual age (BPD), any sepsis (with maximal CRP and duration of antibiotic), cerebral ultrasound and magnetic resonance imaging (MRI) results (IVH or PVL), seizures, NEC, treatment for PDA and postmenstrual age (PMA) for transfer from intermediate to the step-down unit in the NICU.At discharge:Variables recorded are: PMA, weight, length, head circumference and mode and type of nutrition. At St. Olav’s Hospital, families living less than 30 minutes by car from the hospital are offered home care with gavage feeding for infants from PMA 34 weeks. Criteria for participation for the infants are: full enteral feeds; no apneas/bradycardias requiring caffeine or monitoring; stable body temperature and positive weight gain. A family is invited to participate in the home care program if there are two caregivers at home during the day and at least one of them speaks Norwegian or English.

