#### Randomization and allocation concealment

The randomization is done after the initial stabilization of the infant (Fig. 1). Infants are stratified by weeks of gestation (28^0^–29^6^ and 30^0^–31^6^). The randomization is conducted using sealed envelopes organized by the Unit for Applied Clinical Research at the NTNU.

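### Continuous first-24-hour outcomes are compared without adjusting for the randomisation stratum, twin pairs or mode of delivery, which gives up some precision at little saving

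*Protocol article*

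**What the plan says.** The secondary-analysis paragraph under Sample size and statistical analyses fixes the methods: "differences between the SSC and SC groups for continuous variables will be analyzed using two-sample" *t* tests, with Mann-Whitney for non-normal data. For binary outcomes, "Categorical variables will be analyzed by the Pearson chi-square test" or Fisher's exact test. No covariate, stratum or cluster term appears.

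Elsewhere the article gives the design features that these tests leave out:

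- Randomization and allocation concealment: "Infants are stratified by weeks of gestation", in two bands. Randomisation follows initial stabilisation, so mode of delivery is already known.
- Study population: infants "delivered either vaginally or by C-section" are eligible, and twins receive the same allocation.
- Clinical registration: the CRF background data include "mode of delivery, GA, sex, Apgar scores at 1, 5 and 10 minutes, birthweight".
- Intervention: SSC is given "in the delivery room after vaginal delivery, or in the recovery room after C-section", while control infants go to the NICU in an incubator.
- Project context: the delivery rooms and the NICU are on different floors, whereas "The operating room and the postoperative ward are in the same building and at the same floor as the NICU".

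Table 1 schedules temperature, heart rate, respiration and saturation from 15 minutes after birth. These serve the secondary aim on physiological stability in the first 24 hours.

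**The concern.** Mode of delivery is a genuine baseline variable: treatment cannot affect it, and it is recorded for every infant. The article describes different early surroundings by mode of delivery in both arms, so it may well predict temperature and other early measurements. If it does, an unadjusted test leaves its variance in the error term, and any chance difference in C-section share shifts the estimate.

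The gestational-age stratum and the twin pairs raise a related point. Both were built into the allocation and neither enters the analysis. To the extent that stratification balances a prognostic factor between arms, an unadjusted standard error is too large. Treating twins as independent tends to make it too small.

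At stake is the precision of the early stability comparisons. The primary outcome is not at issue.

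**Working it through.** **The plan's own figure.** Difference 7.5, SD 15, power 80%, α = 0.05 (taken as two-sided):

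n = 2 × (1.96 + 0.842)² × 15² / 7.5² = 62.8, so 63 per group by the normal approximation. The *t*-based solution is 63.8, so 64, as stated. Planning 68 allows a loss of 1 − 64/68 = 5.9%. The sample size is not in dispute, and 68 per arm is used below.

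**Assumptions.** The documents give no C-section share p and no effect d of mode of delivery on any early outcome. I take p = 40 to 60% for the imbalance range and d = 0.2 to 0.8 SD.

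**Chance imbalance in C-section share.** The 95% range is ±1.96 × √(2p(1−p)/68).

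- p = 0.5: 1.96 × √(0.50/68) = 0.168.
- p = 0.4 or 0.6: 1.96 × √(0.48/68) = 0.165.

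That is about ±17 percentage points. An exact hypergeometric calculation with p = 50 to 70% gives a probability of about 0.22 to 0.26 for an imbalance of at least 10 points, and 0.05 to 0.06 for at least 15 points. Twins widen this. If a fraction f of infants are twins who share mode and allocation, the variance grows by about 1 + f. With f = 0.3 (assumed), 16.8 × √1.3 = 19 points.

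**Precision.** With d in units of the total SD and p = 0.5, R² = 0.25 × d². The gain in effective sample size is 1/(1 − R²) − 1. The 95% chance shift is 0.168 × d, set against an unadjusted SE of √(2/68) = 0.171 SD.

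| d (SD) | R² | Gain | 95% chance shift |
|---|---|---|---|
| 0.2 | 0.01 | 1% | 0.034 SD = 0.2 SE |
| 0.5 | 0.0625 | 7% | 0.084 SD = 0.5 SE |
| 0.8 | 0.16 | 19% | 0.134 SD = 0.8 SE |

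If d is instead measured in within-mode SDs, 68 per arm acts like 68.7, 72.2 and 78.9 at p = 0.5: gains of 1%, 6% and 16%.

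**Simulation** (68 per arm, independent infants, p = 0.6, 10,000 runs, true effect 0.485 within-mode SD):

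| d (SD) | Type I error, unadjusted / adjusted | Power, unadjusted / adjusted |
|---|---|---|
| 0.2 | 0.051 / 0.051 | 0.804 / 0.806 |
| 0.5 | 0.053 / 0.054 | 0.775 / 0.796 |
| 0.8 | 0.048 / 0.050 | 0.746 / 0.805 |

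**Binary safety events.** If hypothermia risk differs between modes by 10 points (5% v 15%, or 10% v 20%), the adjusted SE is about 0.99 of the unadjusted SE. With 20 points (10% v 30%, or 20% v 40%) it is about 0.97 to 0.98. The saving is therefore about 1 to 3% in SE.

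The effects of the stratum and of twin clustering are not quantified: the documents give no twin share, within-pair correlation or association with gestational age.

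**The case against.** The strongest reply is that nothing here is an error. Two-group tests are valid for a randomised comparison, mode of delivery is not a stratification factor, and the choice of prognostic covariates is often left to the analysis plan, which is not shown. As regards mode of delivery, the first two points stand. A reader might infer that the early comparisons are biased or confounded by it. They are not: randomisation balances it in expectation, and type I error stays near 5%. Lost precision and chance imbalance are also one quantity. The variance due to imbalance, d² × 2p(1−p)/68, divided by the unadjusted variance, 2 × SD²/68, is exactly R², so the ordinary confidence interval already allows for it.

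A reader might also infer that the safety conclusion is weakened. The documents do not support this. The safety outcomes are binary, adjustment would barely change their SE, and an exact test is sensible when events are rare.

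The mechanism has limits. The floor layout is given for one hospital only, and the Trial status section announces two more without describing theirs. Nothing in the article links transfer route to temperature. The place of SSC and the control transfer each act in one arm, so they may point to an effect that differs by mode; a main-effect covariate averages over that and does not test it.

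What does not stand is that this is merely missing detail. The article names specific unadjusted tests, so a stated method can be compared with a better one that uses data already collected.

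**Conclusion.** The point holds as a low-priority improvement for continuous outcomes of the first 24 hours. The stated tests leave out the randomisation stratum, twin pairing and a recorded baseline variable that plausibly predicts early measurements. For mode of delivery, adjustment would be worth roughly 1 to 19% more infants, and the lower end is as credible as the upper. That range rests entirely on an assumed effect of 0.2 to 0.8 SD and a C-section share near one half. If mode of delivery is not prognostic, nothing is gained from it and almost nothing is lost. The gain for the 2-year Bayley is probably negligible, and no useful gain is claimed for the binary safety events.

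The statement that the tests remain valid concerns mode of delivery only. It does not extend to treating twins as independent, which is a reason in itself to cluster by mother.

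**What to change.** Leave randomisation and sample size unchanged. Before outcomes are compared by arm, prespecify the following:

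- For continuous first-24-hour outcomes (temperature, heart rate, respiration, saturation, glucose, blood pressure): linear regression on arm, gestational-age stratum and mode of delivery, with standard errors clustered by mother. Report the adjusted mean difference with its 95% CI.
- For clearly non-normal measures such as saturation: a rank-based or transformed sensitivity analysis, so that the purpose of the Mann-Whitney provision is kept.
- For rare binary safety events: keep the exact test and show counts by mode of delivery descriptively.

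The cost is wording in the analysis plan, two covariate degrees of freedom and slightly more analysis work. No new data are needed. Prespecifying also prevents a choice of covariates after an imbalance has been seen.
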